
**Fig. 1 Fig1:**
[figure not shown]
The schedule of enrolment, interventions, and assessments

**Fig. 2 Fig2:**
[figure not shown]
Flow chart of the intervention

### Plans for participant retention and adherence to the diet

To control the adherence to the diet by the participants, once every 2 weeks, food record questionnaires will be completed 3 days (two normal days and one day off) a week. Researchers will make regular phone calls to participants to reinforce what they will be doing and to encourage them to continue. Also, participants will be monitored in weekly phone interviews. The data of subjects who discontinue or deviate from intervention protocols for any reason will be analyzed with intention-to-treat.

### Criteria for discontinuing or modifying allocated interventions

The criteria for discontinuing allocated interventions for a given trial participant include the following: calorie intake below 80% or above 110% of their recommended calorie, experiencing a severe emotional crisis during the study, and getting pregnant during the study.

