### Intervention

The flow chart of the intervention is shown in Fig. 2. In this study, 56 participants will be selected from the Health Centers of Kashan University of Medical Sciences by Simple Random Sampling according to the inclusion and exclusion criteria. Eligible participants will be stratified by age and BMI to ensure between-group homogeneity. Participants per stratum will be assigned to one of the two groups “modified intermittent fasting” (intervention) and “daily calorie restriction” (control) after baseline investigations. All participants will be required to follow their diet which is prescribed for 8 weeks based on their group and daily energy requirements. The energy requirements for the individuals will be calculated using the Mifflin equation [18]. Intermittent fasting will involve alternating periods of feeding and fasting, on an every-other-day basis (subjects will consume only 25% of the recommended calorie intake on the fasting days and then will consume 100% of the calculated daily energy requirements on feeding days). At midnight each day, the fast and feed days will begin. All fast day meals will be consumed as lunch between 12.00 pm and 2.00 pm to ensure that each subject will be undergoing the same duration of fasting. Participants will be permitted to drink energy-free beverages (such as water, tea, and green tea), coffee without sugar (<400 mg caffeine daily), and non-starchy vegetables (such as lettuce, green leaf, cucumber, and tomato). They will be encouraged to consume plenty of water. On feeding days, the participants will be provided foods at 100% of the calculated daily energy requirements (three main meals and three snacks) and will be advised to eat breakfast at 8:00, lunch at 13:00, and dinner at 20:00. Additionally, participants will be advised to have the first snack at 10:00, the second snack at 16:00, and the last snack at 22:00. The control group daily will consume 63% of their energy requirement (three main meals and three snacks) and will be advised to eat breakfast at 8:00, lunch at 13:00, and dinner at 20:00. Also, the first snack should be eaten at 10:00, the second snack at 16:00, and the last snack at 22:00. Both groups will follow their diet for 8 weeks. Control and intervention group subjects must prepare all their meals at home. All subjects in the two groups will be asked to keep their regular physical activity throughout the study. Daily dietary carbohydrates, fat and protein will account for 55, 30, and 15% of energy requirement, respectively. All participants will have the same number of contacts with the dietician at the on-site visits and phone visits for questions. Implementation adherence will assess by a food record questionnaire. It will be completed by the participants once every 2 weeks, 3 days (2 days/week and 1-day weekend) a week. If the total caloric intake of patients will be between 80 and 110% of the prescribed, there will be adequate adherence [19]. The following will be prohibited during the study: taking a special diet, taking a special supplement or medicine. An overview of the study design, interventions, and assessments to be conducted during the study and their timing is presented in Fig. 1 (enrolment, interventions, and assessments) and Fig. 2 (flow chart of the intervention).

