We propose to use two analysis sets; the intention-to-treat set, considering all patients as randomized regardless of whether they received the randomized treatment, and the “per protocol” analysis set. Given our expectation that very few patients will crossover or be lost to follow-up, these analyses should agree very closely. We will report reasons for withdrawal for each randomization group and compare the reasons qualitatively. The effect that any missing data might have on results will be assessed via sensitivity analysis of augmented data sets. Dropouts (essentially, participants who withdraw consent for continued follow-up) will be included in the analysis by regression imputation method for missing data. This will be accomplished using a set of repeated imputations created by predictive models based on the majority of participants with complete data. After the imputations are completed, all of the data (complete and imputed) will be combined and the analysis performed for each imputed-and-completed dataset. Rubin’s method of multiple (i.e., repeated) imputation will be used to estimate the treatment effect. No interim analyses will be performed.

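### Calorie intake outside 80–110% is made a reason to stop the allocated diet, so a modest lapse in adherence takes a woman off it, and the reference intake is loosely worded

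*Protocol article*

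**What the plan says.** The band of 80 to 110% appears twice in the protocol article.

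- **Intervention** uses it to define adherence: "If the total caloric intake of patients will be between 80 and 110% of the prescribed, there will be adequate adherence". No action is attached to falling outside it.
- **Criteria for discontinuing or modifying allocated interventions** attaches an action. It opens with "The criteria for discontinuing allocated interventions for a given trial participant include the following", and its first item is "calorie intake below 80% or above 110% of their recommended calorie". The other items are a severe emotional crisis and pregnancy. The heading also mentions modifying the intervention, but the sentence speaks only of discontinuing it.

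The diets are set out under Intervention. Women are to "follow their diet which is prescribed for 8 weeks based on their group and daily energy requirements". In the fasting arm, "subjects will consume only 25% of the recommended calorie intake on the fasting days", and feeding days are at 100% of the calculated requirement. For the comparator, "The control group daily will consume 63% of their energy requirement". Intake is measured by a three-day food record every two weeks.

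Two further statements matter. The section on retention and adherence has staff telephone participants to encourage them to carry on, and adds: "The data of subjects who discontinue or deviate from intervention protocols for any reason will be analyzed with intention-to-treat". Statistical assessment defines the intention-to-treat set as "considering all patients as randomized regardless of whether they received the randomized treatment" and also plans a per-protocol set.

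**The concern.** An adherence band describes how well a diet was followed. Here it also decides whether the diet continues. A woman just outside the band is still largely on her allocated diet. If the protocol then stops it, the trial itself ends a partial exposure that support might have kept going.

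Intention-to-treat keeps her data, but no analysis can restore exposure that the protocol has withdrawn. The comparison of women as randomized would then include women taken off their diet by rule, not by their own choice or for their safety.

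The second, smaller matter is the base of the percentage. The stopping rule refers to recommended calories and the adherence definition to prescribed calories. The Intervention section uses *recommended* for the base of which a fast day is 25%, that is, the full requirement. Staff who applied that usage to the stopping rule would get an absurd result.

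**Working it through.** **Inputs** (all from Intervention, as % of calculated energy requirement): fast day 25, feeding day 100, control day 63, band 80 to 110%. No sample-size figure enters this check.

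**1. Planned deficits**

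- Control: 100 − 63 = 37 points.
- Fasting, over one fast-feed pair: mean intake (25 + 100)/2 = 62.5, so the deficit is 37.5 points.

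**2. How far from the diet is a woman at the limits?** Here the band is applied to the prescribed intake.

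| Arm | Limit | Intake | Deficit | Share of planned deficit |
|---|---|---|---|---|
| Control | 110% | 63 × 1.10 = 69.3 | 30.7 | 30.7/37 = 0.83 |
| Fasting (pair) | 110% | 62.5 × 1.10 = 68.75 | 31.25 | 31.25/37.5 = 0.83 |
| Control | 80% | 63 × 0.80 = 50.4 | 49.6 | 49.6/37 = 1.34 |
| Fasting (pair) | 80% | 62.5 × 0.80 = 50.0 | 50.0 | 50.0/37.5 = 1.33 |

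A woman just over the upper limit still has about 83% of her planned deficit when the rule stops her diet. A woman just under the lower limit has about a third more deficit than planned. These are within-arm figures and do not measure the difference between the arms.

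**3. What a perfectly compliant woman scores under each reading of the reference.** Let k be the number of fast days among the three recorded days. Mean intake in the fasting arm is (25k + 100(3 − k))/3.

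| Compliant record | Mean intake, % of requirement | Reference: full requirement | Reference: 62.5 cycle average (fasting arm) | Reference: prescribed for those days |
|---|---|---|---|---|
| Control | 63 | 63: outside | not applicable | 100: inside |
| Fasting, k = 0 | 100 | 100: inside | 160: outside | 100: inside |
| Fasting, k = 1 | 75 | 75: outside | 120: outside | 100: inside |
| Fasting, k = 2 | 50 | 50: outside | 80: on the edge | 100: inside |
| Fasting, k = 3 | 25 | 25: outside | 40: outside | 100: inside |

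Only the last reference, matched to the recorded days, gives 100% for full compliance in both arms. Day by day it allows 20 to 27.5% of requirement on fast days, 80 to 110% on feeding days and 50.4 to 69.3% in controls. The stopping rule does not state this reference.

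**The case against.** **The two sections do not contradict each other.** One defines adequate adherence and the other states a consequence. A reader might infer a conflict, but a label and an action can coexist, and Intervention does not say that the band serves only as a label. This stands: the problem is the action chosen, not an inconsistency.

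**The wording is probably a synonym.** Both sections use the same limits, and the diet is said to be prescribed by group. A reader might infer that the rule would really stop every compliant control. The documents do not support that, because such a rule could not be operated and the prescribed intake is much the likelier meaning. The calculation on the full requirement shows only why the phrase should be tightened.

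**Intention-to-treat already anticipates stopped diets.** This is true, and women who are stopped stay in the analysis, so no loss of numbers follows automatically. It does not remove the dilution, which arises in the conduct of the trial.

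**Stopping may come only after support has failed.** The regular calls and weekly telephone interviews make that plausible. How many records trigger the rule is operational detail that an article may leave to the full protocol. The criterion as stated nevertheless makes non-adherence in itself a ground for stopping.

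**A low limit may protect safety.** A control below 80% of her prescription eats less than 50.4% of requirement. The protocol gives no such rationale, but the fix keeps room for it.

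**A power loss is tempting to calculate.** A reader might infer one by assuming a share of women stopped and no remaining effect in them. The documents give neither the share nor what a woman eats after stopping, and weeks already spent on the diet would count for something. The answer also depends on whether one takes 23 or 28 women per group, given that stopped women are retained. No figure can be defended.

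**Conclusion.** The point holds as a minor design weakness. The protocol makes non-adherence alone a criterion for ending the allocated diet, at a threshold where women in either arm still have about 83% of the planned energy deficit on the upper side. That pulls against the plan to encourage women to continue, and it can dilute the as-randomized comparison.

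The 83% rests on the prescribed percentages and on reading the band against prescribed intake. For the fasting arm it is averaged over one fast-feed pair. The size of any dilution cannot be derived from the documents. The loose reference term is a drafting fault with a very probable intended meaning, and it does not show that compliant women would in fact be stopped.

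**What to change.** In both Intervention and the discontinuation section, define the reference once: the calories prescribed for the same recorded days, that is, 25% or 100% of requirement in the fasting arm according to day type, and 63% in the control arm.

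Use the 80 to 110% band only to report adherence and to define the per-protocol set that is already planned. Delete it from the discontinuation criteria. Keep discontinuation for pregnancy, severe emotional crisis or a clinical safety reason, including unsafely low intake as judged by the clinical team. Women outside the band then stay on their diet with the telephone support already planned.

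The cost is wording in two sections and a mark for fast or feed day on the existing food record. No extra visits or participants are needed, and the sample size does not change.

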### Roles and responsibilities

This study will be conducted in Shahid Beheshti Hospital, Kashan. The trial will be run on an individual basis by the principal investigators. The study will be overseen by the scientific committee every week or when the need arises, in case of any adverse events. Kashan University of Medical Sciences will oversee the overall conduct of the trial. The study team will meet and discuss the problems in the operation of the study every week. DMC will be not needed for the study as the study will involve a small group of patients and will be in a single center.

### Data management and confidentiality

Data will be stored in SPSS software and kept in local storage as well as in cloud storage. Although patients will have to provide their full names and contact details on the consent form, proper measures will be taken to protect their confidentiality. Their names will be replaced with a unique number that will be pasted onto their consent forms and their completed survey questionnaires. Results will be reported in aggregate. The data will not contain any personal information of the participants. Although every effort will be made to keep study records private, in some cases, patient information in this research study can be reviewed by representatives of the University for purposes such as quality control or safety.

## Assessment of variables

### Sleep quality and sleep disturbances

The PSQI evaluates self-reported sleep disturbances and quality in the previous 4 weeks. PSQI measures 7 components of sleep and has 19 items: subjective sleep quality, sleep duration, sleep latency, use of sleeping medication, sleep disturbance, daytime dysfunction, and habitual sleep efficiency [20]. These items are rated in terms of the severity of the problem or frequency on a 4-point Likert scale (not during the past month: 0, less than once a week: 1, once or twice a week: 2, three or more times a week: 3). Each component score has a range of 0 to 3, with greater scores indicating lower sleep quality. The component scores sum yields a PSQI global score which ranges from 0 to 21. Higher scores express worse sleep quality. Statistical analyses also support looking at three factors, which include perceived sleep quality (using sleep latency, subjective sleep quality, and sleep medication variables), sleep efficiency (using sleep efficiency and sleep duration variables), and daily disturbances (using daytime dysfunctions and sleep disturbances variables). The PSQI has the same problems as other self-report inventories in that scores can be minimized or exaggerated by the person completing them [20].

### Sleepiness

The ESS measures daytime sleepiness. It is a self-reported questionnaire where individuals answer questions based on how likely they are to doze off or fall asleep during sedentary activities. It is an attractive alternative to objective methods of assessing sleepiness. ESS has eight items and includes a respondent format “would never doze” = 0, “slight chance of dozing” = 1, “moderate chance of dozing” = 2, and “high chance of dozing” = 3. A total score is calculated by summing the scores of the eight items, ranging from 1 to 24 points with higher values reflecting a higher level of sleepiness. The change score is calculated as the change between the total ESS score at baseline and follow-up [21].

### Insomnia

The Insomnia Severity Index has seven items that evaluate the severity of sleep-onset (initial), early morning awakening (terminal) problems, sleep maintenance (middle), satisfaction with current sleep pattern, noticeability of impairment attributed to the sleep problem, interference with daily functioning, and level of distress caused by the sleep problem. Each item is rated on a 0–4 scale (0 indicating no problem and 4 indicating a very severe problem) with a total score ranging from 0 to 28. The Insomnia Severity Index total scores are categorized as 0–7: not clinically significant insomnia; 8–14: subthreshold insomnia; 15–21: moderate insomnia; and 22–28: severe insomnia [22].

### Physical activity scale

The questionnaire of physical activity based on the metabolic equivalents (MET) will be used to measure physical activity in this study, which includes 9 levels of activity from sleep and rest (METs = 0.9) to intense activity (more than 6 METs) [23].

### Anthropometric indices

A stadiometer (accuracy of 0.5 cm) will be used to measure the Height. Individuals’ weight, with a light dress and without shoes, will be measured by using the scale (accuracy of 0.1 kg). BMI will be calculated as weight (kg) divided by height squared (m^2^). The waist-to-hip ratio will be calculated as the waist circumference divided by the hip circumference. The waist circumference will be measured at the midpoint between the iliac crest and lowest rib, by using a non-stretchable measuring tape during normal expiration [24]. The hip circumference will be horizontally measured at the widest portion of the buttocks [24]. Other anthropometric indices such as extracellular water ratio, visceral fat area, percent body fat, fat-free mass, body fat mass, soft lean mass, skeletal muscle mass, and total body water will be evaluated by Inbody770 model BPM040S12FXX. All anthropometric indices will be measured at the beginning and end of the study.

### Statistical assessment

To investigate if the data follows a normal distribution, we will use the Kolmogorov-Smirnov test. To compare qualitative data between the two groups, a chi-square test will be used. An independent t-test will be used to determine differences in quantitative data between groups. In non-parametric conditions and parametric conditions, the Wilcoxon test and paired *t*-test, respectively, will be used to compare the mean of quantitative variables within the group before and after the intervention. To compare the mean between the two groups, the Mann-Whitney test and *t*-test for non-parametric conditions and parametric conditions, respectively, will be used. Analysis of covariance will be utilized to determine the difference in data changes between the 2 groups at the end of the study. The adjusted *p-*values corresponding to each statistical test will be used to investigate the intervention effects by using the Bonferroni correction to analyze multiple outcomes. Data analysis will be done with SPSS software. We plan to conduct two subgroup analyses, both with strong biological rationale and possible interaction effects. Multiple regression model and analysis of covariance (ANCOVA) will be used to evaluate whether specific variables are confounders for the treatment effect and whether the treatment effect interacts with specific covariates.

We propose to use two analysis sets; the intention-to-treat set, considering all patients as randomized regardless of whether they received the randomized treatment, and the “per protocol” analysis set. Given our expectation that very few patients will crossover or be lost to follow-up, these analyses should agree very closely. We will report reasons for withdrawal for each randomization group and compare the reasons qualitatively. The effect that any missing data might have on results will be assessed via sensitivity analysis of augmented data sets. Dropouts (essentially, participants who withdraw consent for continued follow-up) will be included in the analysis by regression imputation method for missing data. This will be accomplished using a set of repeated imputations created by predictive models based on the majority of participants with complete data. After the imputations are completed, all of the data (complete and imputed) will be combined and the analysis performed for each imputed-and-completed dataset. Rubin’s method of multiple (i.e., repeated) imputation will be used to estimate the treatment effect. No interim analyses will be performed.

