## Methods/design

### Study design and participants

This is a randomized, controlled, parallel-group trial to compare the effect of a modified intermittent fasting diet and daily calorie restriction diet on sleep quality and anthropometric indices in women with obesity or overweight over 8 weeks. The framework of the trial is superiority. Participants will be selected from the Health Centers of Kashan University of Medical Sciences by simple random sampling. Participants will be randomly assigned into two groups, daily calorie restriction (control) and fasting (intervention). The protocol was approved by the Ethics Committee of Kashan University of Medical Sciences (IR.KAUMS.MEDNT.REC.1401.046) and was registered at the Iranian Registry of Clinical Trials (IRCT20220522054958N3). All participants will give written consent before any study-related procedure. Inclusion criteria include obese or overweight (40 >BMI ≥25) women between 18 and 50 years old. Exclusion criteria include breastfeeding; pregnancy; having chronic diseases such as heart disease, hypertension, diabetes, and gastrointestinal disorders; smoking; weight loss of 1 to 2 kg in the past month; alcohol abuse; following a specific diet or taking a specific medication; overnight shifts; taking dietary supplements; and having mental or psychological diseases. The obese or overweight (40 >BMI ≥25) women between 18 and 50 years old will be included in the study, provided they meet the inclusion criteria.

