### Sample size calculation

We based our sample size calculation on fat-free mass (FFM) data of a previously published randomized controlled trial [17]. The mean and standard deviation of FFM were 63.4 and 3.4 (kg) in the intervention group and 66.9 and 4.9 (kg) in the control group. To detect a clinically significant difference in the outcome measures (sleep quality, daytime sleepiness, insomnia, BMI, FFM, body fat mass, waist circumference, waist-to-hip ratio, hip circumference, the visceral fat area, percent body fat, soft lean mass, skeletal muscle mass, extracellular water ratio, and total body water) with an alpha error of 5% and power of 80%, 23 women will be needed in each group. We presume a drop-out rate of 20%, based on clinical study experience, and thus 28 women will be recruited in each group.$$n=\frac{{\left(Z1-\frac{\alpha }{2}+Z1-\beta \right)}^2\left({\sigma}_1^2+{\sigma}_2^2\right)}{\left({\mu}_1-{\mu}_2\right)}$$

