## Outcome measures

### Primary outcomes

The primary outcomes of the study are the differences between the two groups with regard to the changes from baseline values in the following variables: Pittsburgh Sleep Quality Index (PSQI), Epworth Sleepiness Scale (ESS), Insomnia severity index, BMI, FFM, body fat mass, waist circumference, and the waist-to-hip ratio.

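### The Bonferroni family is not stated, so the threshold for a primary outcome is 0.00625 or 0.0033; fixing the family at the eight primaries and using Holm closes the gap at almost no cost

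*Protocol article*

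**What the plan says.** All references are to the protocol article.

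- **Primary outcomes** lists eight between-group differences in change from baseline: "Pittsburgh Sleep Quality Index (PSQI), Epworth Sleepiness Scale (ESS), Insomnia severity index, BMI, FFM, body fat mass, waist circumference, and the waist-to-hip ratio". Three are sleep scales and five are body measures. **Secondary outcomes** lists seven more body measures.
- **Study design and participants** states: "The framework of the trial is superiority".
- **Statistical assessment** says that adjusted p-values, attached to each test, will be used to judge the intervention effects "by using the Bonferroni correction to analyze multiple outcomes". It gives no number of comparisons and does not name the family.
- **Sample size calculation** puts all 15 outcomes in one list, and says that "with an alpha error of 5% and power of 80%, 23 women will be needed in each group".
- **Anthropometric indices** shows that some outcomes are tied by construction. For example, "The waist-to-hip ratio will be calculated as the waist circumference divided by the hip circumference", and BMI is computed from weight and height.

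**The concern.** Bonferroni has one parameter, the number of hypotheses in the family, and the article leaves it open. Two readings fit the text. The separate lists of primary and secondary outcomes suggest a family of eight. The single list of 15 in the sample size section suggests a family of 15. The wording that attaches adjusted p-values to each test could reach further still, because the same section also describes within-group tests and analysis of covariance.

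The choice changes conclusions. A primary outcome with p = 0.005 passes on the first reading and fails on the second, and nothing in the article settles which applies. A rule that can be completed after the results are known gives less protection than it appears to.

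A second, smaller matter is efficiency. With eight hypotheses tested together, single-step Bonferroni is never more powerful than Holm's step-down version, and both need the same p-values.

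**Working it through.** **Inputs.** From the sample size section: "The mean and standard deviation of FFM were 63.4 and 3.4 (kg) in the intervention group and 66.9 and 4.9 (kg) in the control group"; two-sided 5%; power 80%; 23 evaluable women per group. From the outcome sections: 8 primary and 7 secondary outcomes. The article gives neither the correlations between outcomes nor the number of true effects. I assume a common correlation of 0, 0.5 or 0.8, and one, four or eight true effects of equal size.

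**1. The plan's own figure.** n = (z₀.₉₇₅ + z₀.₈₀)² (s₁² + s₂²) / (μ₁ − μ₂)²
= (1.960 + 0.842)² × (3.4² + 4.9²) / 3.5²
= 7.849 × 35.57 / 12.25 = 22.8, so 23 per group. This reproduces the stated number, with the difference squared in the denominator and an undivided two-sided 5%.

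**2. Thresholds.**
- Family of 8: 0.05/8 = 0.00625, critical value 2.734.
- Family of 15: 0.05/15 = 0.00333, critical value 2.935.
- The decision is open for 0.0033 < p ≤ 0.00625.

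**3. Power per outcome under Bonferroni.** An outcome with 80% power at an unadjusted 5% has noncentrality 1.960 + 0.842 = 2.802. Power is Φ(2.802 − critical value).
- Family of 8: Φ(0.067) = 53%.
- Family of 15: Φ(−0.134) = 45%.

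**4. Holm over the eight primaries.** Order the p-values and compare the smallest with 0.05/8, the next with 0.05/7, and so on up to 0.05, stopping at the first failure. Every threshold is at least 0.05/8, so Holm rejects everything that Bonferroni rejects. Simulated power per truly different outcome (200,000 replicates, normal statistics, noncentrality 2.80):

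| Truly different outcomes | Bonferroni over 8 | Holm over 8 |
|---|---|---|
| 1 | 53% | 53% |
| 4 | 53% | 56% |
| 8 | 53% | 62–64% |

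The range in the last row runs from correlation 0.8 (62%) to 0 (64%).

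**5. What Holm does not change.** Its first step is the same 0.05/8, so at least one rejection occurs under Holm exactly when it occurs under Bonferroni. Two consequences follow.
- The chance of at least one rejection is equal. With all eight different and correlation 0.5, it is about 90% for both.
- With no true effects, the family-wise error is equal: about 3.9% for both at correlation 0.5 and 2.5% for both at 0.8. The part of the 5% left unused because outcomes are correlated stays unused.

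**6. Sample size at the divided alpha.** For 80% power per outcome, the formula in step 1 gives (2.734 + 0.842)² × 35.57 / 12.25 = 37.1, so 38 per group for a family of 8. For a family of 15 it gives (2.935 + 0.842)² × 35.57 / 12.25 = 41.4, so 42. The plan has 23 evaluable ("28 women will be recruited in each group").

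**The case against.** **Bonferroni is a sound choice.** It is prespecified, holds under any dependence, and gives simple simultaneous confidence intervals, which Holm does not readily give. This stands. Choosing Bonferroni is conservative and is not an error, so the case for Holm is one of efficiency only.

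**The gain is modest.** Of the 27 points lost from 80%, Holm returns 0 to 11. The top of that range needs all eight outcomes, including the three sleep scales, to have the standardized effect assumed for fat-free mass. This also stands. A reader might infer that Holm recovers the error rate wasted on tied outcomes such as BMI and fat mass, or restores the planned power. Steps 4 to 6 show that it does neither.

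**The family may be set out in a statistical analysis plan that is not shown.** That is possible. But the article states the rule itself, and its pooled list of 15 outcomes pulls against its separate primary and secondary lists. The ambiguity is in the published text, and one phrase would remove it.

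**Stronger readings that the article does not support.** A reader might conclude that the plan disregards its primary/secondary division. It is silent on whether that division defines the family, and a family of eight is a fair reading. A reader might also conclude that one positive outcome in eight would establish superiority of the diet as a whole. The article says only that the framework is superiority. It defines the primaries variable by variable and adjusts p-values test by test, which fits outcome-by-outcome claims. Finally, family-wise error would exceed 5% if primaries and secondaries were corrected as two separate families and both supported claims, but the article does not describe such a scheme.

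**Conclusion.** The concern holds in a limited form. The multiplicity rule lacks its family, so the decision on any primary outcome with p between 0.0033 and 0.00625 is open after the data are seen. Per-outcome power is 53% or 45% depending on the reading. Once the family is fixed, Bonferroni controls the error. Holm over the eight primaries would do so equally and would add about 3 points of per-outcome power if four outcomes differ, 9 to 11 if all eight do, and none if only one does. The thresholds are exact. The power figures rest on a noncentrality of 2.80 for every truly different outcome and on assumed correlations. The mismatch between a sample size at an undivided 5% and an analysis at a divided one is a separate point, which Holm does not resolve.

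**What to change.** In **Statistical assessment**:

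1. State that the confirmatory family is the eight primary outcomes.
2. Replace Bonferroni with Holm's step-down procedure at a two-sided family-wise 5%.
3. State that the seven secondary outcomes are exploratory and are reported as estimates with 95% confidence intervals.
4. State that superiority is claimed only for each primary outcome that passes Holm, with sleep and body-composition conclusions reported separately.

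The cost is a few sentences and a trivial calculation on the same p-values; no patients, visits or data are added. There are two downsides. Secondary outcomes carry no confirmatory claim, and simultaneous intervals that match Holm are less simple than Bonferroni's. If simple intervals matter more to the investigators, Bonferroni over a stated family of eight would also settle the open threshold, at the power shown above. The sample size needs its own reconciliation with the alpha actually used.
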